### Power calculation

On the basis of the Cochrane review by Murray et al. [37] we expect a small effect on the primary outcomes (Cohen’s d = 0.2). To detect a small effect with an α of 0.05 a power of 0.80 (one-tailed t-test), a sample size of N = 310 (155 per group) is required. Expecting a dropout 20% between registration and follow-up (3 months), we aim at including a sample of N = 414 at baseline.

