### Aims of the trial

The study evaluates an IHCA with information on chronic low back pain (CLBP), pain management education and decision support in a dialogue-based, tailored format against a standard website showing identical information without dialogue or tailoring. The primary hypothesis is that the dialogue-based, tailored format has larger effects on CLBP knowledge and patient empowerment than the standard website. Exploratory research questions are if usage is higher for the dialogue-based, tailored format and whether users feel better prepared for the consultation and, when facing a health decision, experience less decisional conflict after using the dialogue-based, tailored site rather than the standard website.

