#### Intervention condition

The format of the website in the intervention condition tries to imitate a real conversation (dialogue-based) with a health professional, tailoring the content and tone of the dialogue to relevant patient characteristics. tunnelled design where the user proceeds through the content with a predetermined chronology was implemented in the intervention condition because such a design found to increase website use and knowledge gained from a website [20]. However, a tunnelled website might also evoke resistance [21], which is why we decided to give the user some degree of freedom over the chronology through the dialogue. Each information block ends with questions where the user can choose one of at least three reply options and receives a tailored answer. These tailored answers reflect the option the user has chosen using an empathic and appreciative intonation and build a personalized bridge to the next information block.

The concepts of coping style according to the avoidance-endurance model (AEM) [22] and health literacy (CLBP knowledge and preferred detailedness of information) were used for tailoring the provided information to individual preferences of the users. The individual coping style was assessed by using a questionnaire which is presented before starting the dialogue. There are four AEM subtypes: the “depressed endurer” (high endurance coping (EC) and high depressiveness (D)), the “happy endurer” (high EC and low D), the “depressed avoider” (low EC and high D), and the “adaptive coper” (low EC and low D; for examples see Table 1). During the virtual conversation, the content, the intonation and messages are tailored to the coping style of the individual user. This approach was inspired by Motivational Interviewing [23], a counseling technique used especially to address ambivalence about health behavior change.

**Table 1 T1:** Tailoring to coping style

**Coping type**	**Adaptive coper**	**Happy endurer**	**Depressed endurer**	**Depressed avoider**

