### Statistical analyses

To empirically test the hypotheses, t-tests for independent samples will be calculated. We do not expect confounding factors due to randomizing the participants to the control and intervention condition and the most likely resulting structural equality of these two groups. In case baseline disparities should be detected, they will be taken account of as confounding variables in an analysis of covariance (ANCOVA). By using an intention-to-treat approach in which participants were analyzed in their original randomized groups regardless of the frequency or duration of website use we will include all randomized participants in the analyses in order to avoid biases such as non-random attrition of participants. Additionally we will perform a sensitivity analysis following the per-protocol approach. This will be done by including only participants that have completed all the measurements. A α level of ≤ 0.05 will utilized as the cutoff for statistical significance. With regard to the exploratory research questions, we expect only small sample sizes, hence only a small fraction of the participants will be confronted with the situation of having to make a treatment decision in the course their CLBP. Therefore, only these participants can be asked to fill in the DCS and PDMS. In order to be able to appraise the exactitude of testing, 95% confidence intervals will be defined for all parameters.

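### The trial is sized on a one-tailed 0.05 test but reported with 95% intervals, and 155 per group does not give the stated 80% power on either reading of sidedness

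*Protocol article*

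**What the plan says.** The primary hypothesis, in Aims of the trial, is directional: "the dialogue-based, tailored format has larger effects on CLBP knowledge and patient empowerment than the standard website".

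The Power calculation section takes its effect size from a Cochrane review, "we expect a small effect on the primary outcomes (Cohen’s d = 0.2"), and then gives the design parameters: "To detect a small effect with an α of 0.05 a power of 0.80 (one-tailed t-test"). From these it concludes that "a sample size of N = 310 (155 per group) is required".

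The Statistical analyses section states the test, "t-tests for independent samples will be calculated", and the decision threshold, "A α level of ≤ 0.05 will utilized as the cutoff for statistical significance". Neither statement mentions sidedness. The section closes by saying that "95% confidence intervals will be defined for all parameters", with the stated purpose of judging how exact the testing is.

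The article does not say that the confirmatory tests are one-tailed, that the intervals are one-sided, or why a one-tailed level of 0.05 was chosen.

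**The concern.** One-tailed appears only in the sample-size sentence. The section that holds the decision rule gives a bare 0.05 and a 95% interval for every parameter. A one-tailed 0.05 test pairs with a 90% two-sided interval or a one-sided 95% bound. A conventional 95% interval pairs with a two-sided 0.05 test. If the test follows the power section and the interval follows the analysis section, a result can be called significant and be reported beside an interval that includes no effect. The planned effect of d = 0.2 lies inside the range of observed effects where this happens.

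Sidedness also determines which power figure applies, so the power sentence has to be checked. It does not hold on either reading, and readers would rely on an 80% that the design does not have.

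**Working it through.** **Inputs.** From Power calculation: d = 0.2, α = 0.05, power 0.80, one-tailed t-test, 310 in total (155 per group), 414 at baseline. From Statistical analyses: independent-samples t-test, cutoff 0.05, 95% intervals. Assumption: the 95% intervals are of the usual two-sided kind, which the article does not say.

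**1. Reproducing the plan's sample size.** For two independent groups of equal size, n per group = 2(z₁₋α + z₁₋β)²/d².
- One-tailed 0.05: 2 × (1.645 + 0.842)²/0.04 ≈ 309.1, so 310 per group; with the noncentral t, 309.8 per group, so 310. That is 620 in total.
- Two-sided 0.05: 2 × (1.960 + 0.842)²/0.04 ≈ 392.4, so 393 per group; with the noncentral t, 393.4, so 394. That is 788 in total.

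Neither gives 310 in total. The plan's 310 is the one-tailed requirement for each group. The figure of 155 matches a one-sample or paired one-tailed calculation, (1.645 + 0.842)²/0.04 ≈ 154.6, which is not the planned test.

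**2. Power at 155 per group.** The degrees of freedom are 308 and the noncentrality is 0.2 × √(155/2) = 1.761. The critical values are 1.650 (one-tailed 0.05) and 1.968 (two-sided 0.05).

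| n per group | Power at d = 0.2, one-tailed 0.05 | Power at d = 0.2, two-sided 0.05 | Difference |
|---|---|---|---|
| 155 (as planned) | 54.5% | 41.9% | 12.6 points |
| 207 (all 414, no dropout) | 65.0% | 52.8% | 12.3 points |
| 310 (true one-tailed requirement) | 80.0% | 70.1% | 10.0 points |

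Differences are taken from unrounded powers. At 155 per group, the effect detectable with 80% power is d = 0.283 one-tailed and d = 0.319 two-sided.

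**3. Splitting the shortfall.** From the claimed 80% to 54.5% is 25.5 points, all due to the per-group/total slip. From 54.5% to 41.9% is a further 12.6 points, due to sidedness.

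**4. Where test and interval disagree.** The observed d equals t × √(2/155) = t × 0.1136. One-tailed significance starts at 1.650 × 0.1136 = 0.187. The two-sided 95% interval excludes zero from 1.968 × 0.1136 = 0.224. An observed d from about 0.187 to 0.224 is therefore significant one-tailed with an interval covering zero. At a true d of 0.2 the probability of landing there is 54.5% − 41.9% = 12.6%. It would still be about 10% with 310 per group, so correcting the sample size alone does not remove the conflict.

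**The case against.** The case against has real weight on sidedness. The primary hypothesis is directional and the power section names a one-tailed test, so the two together point to one-tailed testing. Nothing in the analysis section says two-sided; that is inferred from the interval level. The intervals are described as a gauge of exactness, not as a second decision rule, and the article condenses a fuller document. This stands to the extent that it is too strong to say that the sidedness is left open. It does not remove the mismatch: if the tests are one-tailed at 0.05, conventional 95% intervals are the wrong companion to them. A one-sided 95% bound would agree with the test, but the article gives no sign that this is meant.

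Three stronger readings are tempting and are not supported.
- The Intervention condition section notes that "a tunnelled website might also evoke resistance", and a reader might infer that the article foresees a harmful result which its test would then miss. The same sentence goes on to say that users were given some freedom over the sequence for that reason. It describes a risk that was designed against, and does not predict lower knowledge or empowerment.
- A reader might infer that a worse result in the tailored arm could not be reported. A two-sided 95% interval would show it; only a formal significance claim in that direction is lost.
- A reader might charge the whole drop from 80% to 42% to the one-tailed choice. About two thirds of it (25.5 of 38.1 points) comes from the per-group/total slip.

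Nor is a one-tailed test of a directional hypothesis an error in itself. It holds its type I error at 5%, and preferring a two-sided test is a matter of convention.

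**Conclusion.** The point holds in two parts. First, the test used for sizing and the interval planned for reporting are not a matching pair. If the intervals are ordinary two-sided ones, about one trial in eight at d = 0.2 with 155 per group would give a significant one-tailed test with a 95% interval that includes zero. Second, and with the larger consequence, the stated 80% power is wrong on either reading of sidedness. Even if all 414 recruits were analysed, power at d = 0.2 would be about 65% one-tailed and 53% two-sided.

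The calculations assume equal groups, the unadjusted t-test that the article names, and each primary outcome taken by itself at 0.05.

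**What to change.** State the sidedness once and apply it to test, interval and power. Either option is coherent:
- two-sided 0.05 (equivalently one-tailed 0.025) with 95% intervals; or
- one-tailed 0.05 with 90% intervals or a one-sided 95% bound.

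Then replace the power sentence with the figures that 155 analysed per group supports:
- two-sided: 42% at d = 0.2, and 80% at d = 0.32;
- one-tailed: 54.5% at d = 0.2, and 80% at d = 0.28.

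The cost is wording and a less favourable power statement. If 80% power at d = 0.2 is to be kept, wording is not enough. The analysed sample would have to be 620 one-tailed or 788 two-sided, which at the stated 20% dropout means 620/0.8 = 775 or 788/0.8 = 985 at baseline, against the planned 414.

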**Methods/Design:**

The tailored IHCA will be tested regarding effectiveness and usage against a standard website with identical content in a single-blinded randomized trial with a parallel design. The IHCA contains information on chronic low back pain and its treatment options including health behaviour change recommendations. In the intervention group the content is delivered in dialogue form, tailored to relevant patient characteristics (health literacy, coping style). In the control group there is no tailoring, a standard web-page is used for presenting the content. Participants are unaware of group assignment. Eligibility criteria are age ≥ 18 years , self- reported chronic low back pain, and Internet access. To detect the expected small effect (Cohen’s d = 0.2), the sample aims to include 414 patients, with assessments at baseline, directly after the first on-page visit, and at 3-month follow-up using online self-report questionnaires. It is expected that the tailored IHCA has larger effects on knowledge and patient empowerment (primary outcomes) compared to a standard website. Secondary outcomes are website usage, preparation for decision making, and decisional conflict.

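### The 310 participants given as the total needed for 80% power at d = 0.2 are the number needed per group; the 414 target gives about 57% to 65% one-tailed power

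*Protocol article*

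**What the plan says.** The Power calculation section of the protocol article expects Cohen's d = 0.2 on the primary outcomes. At alpha 0.05 it concludes that "a power of 0.80 (one-tailed t-test), a sample size of N = 310 (155 per group) is required". It then allows for 20% dropout between registration and the three-month follow-up and sets a baseline target of 414. The abstract links this target to the same effect size: to detect d = 0.2, "the sample aims to include 414 patients".

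The Study design section describes a two-armed parallel trial. The Statistical analyses section names the test: "t-tests for independent samples will be calculated". There, analysis of covariance is to be used only if baseline disparities are found, and no covariate-outcome correlation is assumed anywhere.

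**The concern.** The total and the per-group number are both written out, so this is not a loose use of N. The figure 310 equals, to the integer, the per-group answer for the stated inputs. If it is a per-group number labelled as a total, the required sample is understated by a factor of two, and the recruitment target has been built on the understated figure.

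The power calculation refers to the primary outcomes together, so the error bears on both CLBP knowledge and patient empowerment. Both arms see the same content and the authors themselves expect a small effect. A non-significant result is therefore quite possible even if the tailored format has the expected benefit, and a reader who relies on the stated 80% could give such a result more weight than the design supports.

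**Working it through.** **Inputs, all from the protocol article.** d = 0.2, alpha = 0.05, one-tailed, power 0.80, 155 per group, 20% dropout and a target of 414 come from Power calculation. The independent-samples t-test comes from Statistical analyses. The two parallel arms come from Study design.

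**1. Reproducing the stated requirement.** For two equal groups, the normal approximation is

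n per group = 2 × (z₀.₉₅ + z₀.₈₀)² / d² = 2 × (1.645 + 0.842)² / 0.2² ≈ 309.1, rounded up to 310.

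The exact noncentral-t solution is 309.8, also 310. The total is 2 × 310 = 620. The plan's 310 is reproduced as a per-group number but not as a total.

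**2. Other routes to a total of 310.**
- Two-sided 5% test: 393.4 per group (exact t), further away.
- One-sample or paired one-tailed t-test: about 156 in total. This is not the planned test and does not give 310.
- Analysis of covariance: the sample shrinks by the factor 1 − r². Going from 310 to 155 per group needs r = √(1 − 155/310) ≈ 0.71. No such correlation is assumed, and the adjustment is only conditional.

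**3. Power for d = 0.2, one-tailed alpha 0.05.** In the normal approximation, power = Φ(d√(n/2) − 1.645). For n = 155 this is Φ(1.761 − 1.645) = Φ(0.116) ≈ 0.546. The exact noncentral-t values are below; the last column is the effect detectable with 80% power.

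| Scenario | n per group | Power | Detectable d |
|---|---|---|---|
| Stated requirement | 155 | 54.5% | 0.28 |
| 414 recruited, 20% lost (414 × 0.80 = 331) | about 166 | 56.9% | 0.27 |
| All 414 analysed | 207 | 65.0% | 0.24 |
| Size that the inputs require | 310 | 80.0% | 0.20 |

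**4. The dropout step.** 310/0.80 = 387.5, so 388. The target of 414 implies a loss of 1 − 310/414 = 25.1%, and 310/0.75 = 413.3, so 414. The target fits 25% dropout, not the stated 20%. For comparison, 620 analysed with 20% dropout would need 620/0.80 = 775 randomised.

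**The case against.** The strongest objection concerns which power figure belongs to the trial. A reader might infer that the trial has about 55% power. That figure belongs to the stated requirement of 155 per group. The plan recruits 414, which at its own 20% dropout leaves about 166 per group. The Statistical analyses section also says that all randomised participants will be analysed, and CLBP knowledge is measured straight after the first visit, so the three-month dropout need not apply to it in full. This objection stands: the planned trial's one-tailed power is about 57% to 65%, and its chance of missing a true d of 0.2 is about 35% to 43%. The gap to 80% remains.

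A second tempting reading is that the statement "95% confidence intervals will be defined for all parameters" commits the trial to a two-sided 5% test, which would lower power to about 44% to 53% at the 414 target. The documents do not support this. The Power calculation section says one-tailed, the primary hypothesis under Aims of the trial is directional, and the intervals are introduced as a gauge of precision. A 95% interval reported beside a one-tailed test does not change the test. The two-sided figures should not be counted towards the size of the error.

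Third, the text does not show how the error arose. A per-group number taken for a total is plausible given the exact match, but it is an inference, and the finding does not depend on it.

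Nor can the point be left to a fuller protocol or an analysis plan. The article prints a complete calculation, and its result does not follow from its inputs.

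**Conclusion.** The power statement is wrong as written. The stated inputs require 310 per group (620 analysed), twice the stated total. The 155 per group tied to 80% power gives about 54%. The 414 target gives about 57% one-tailed with 20% dropout and about 65% if everyone is analysed. No reading of the planned sample reaches 80%.

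The result assumes equal allocation, as the 155 per group implies, and the unadjusted t-test that the plan names. The 65% is an upper figure, because it takes all 414 to contribute outcome data. Separately, 20% dropout and a target of 414 do not agree when the starting point is 310.

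**What to change.** - **Power calculation and abstract:** state that 80% power for d = 0.2 (one-tailed alpha 0.05, independent-samples t-test) needs 310 analysed per group, 620 in total. Keep 414 and say what it delivers: about 57% to 65% one-tailed power for d = 0.2, or 80% power for d of about 0.27 (166 per group) to 0.24 (207 per group). The abstract should no longer present 414 as sized to detect d = 0.2 without that qualification.
- **Dropout sentence:** reconcile the 20% with the target of 414, which corresponds to about 25% loss from 310, and base the restated power on the group sizes that 414 yields under the dropout rate chosen.
- **Statistical analyses (optional):** repeat the one-tailed choice next to the significance level. If a two-sided 5% test is in fact intended, say so and quote the matching power, about 44% to 53%.

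The cost is wording and a less favourable stated power. The correction itself needs no extra patients and no change to the conduct of the trial.

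### The baseline target of 414 does not follow from N = 310 and 20% dropout, which gives 388; 414 corresponds to 25% dropout

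*Protocol article*

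**What the plan says.** The Power calculation section of the protocol article gives its whole derivation in three sentences.

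- Effect: "we expect a small effect on the primary outcomes (Cohen’s d = 0.2".
- Error rates: "with an α of 0.05 a power of 0.80 (one-tailed t-test".
- Requirement before dropout: "a sample size of N = 310 (155 per group) is required".
- Dropout and target: "Expecting a dropout 20% between registration and follow-up (3 months), we aim at including a sample of N = 414 at baseline".

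The Methods/Design part of the abstract repeats the target ("the sample aims to include 414 patients"). The article gives no other dropout rate, inflation factor or safety margin.

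**The concern.** The text presents 414 as the result of allowing for 20% dropout, and it does not come out of that calculation. All the inputs and the result are printed, so this is not a detail left to a fuller protocol or analysis plan.

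What is at stake is a planning figure. A reader cannot tell whether the trial planned for 20% or 25% loss, or whether about 331 or about 310 participants are expected at three months. Retention will be judged against that figure, and the Background and Discussion both treat attrition as a known weakness of online trials. The rate runs from registration to the three-month follow-up. It therefore bears mainly on patient empowerment, which is measured then, and less on knowledge, which is measured after the first visit.

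**Working it through.** **Inputs**, all from the Power calculation section: 310 in total, 155 per group, dropout 20%, target 414, d = 0.2, one-tailed α = 0.05, power 0.80. Equal allocation is implied by 155 per group.

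**1. Trying to reproduce 414 from 310 and 20%.**

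| Rule | Calculation | Result |
|---|---|---|
| Divide by the retained fraction | 310/(1 − 0.20) = 387.5 | 388 (194 per group) |
| Add the percentage | 310 × 1.20 | 372 |
| Apply 20% twice | 310/(0.80 × 0.80) = 484.4 | about 484 |

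None gives 414. The gap from the standard rule is 414 − 388 = 26, which is too large for rounding.

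**2. Which rate gives 414.**

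- Implied dropout: 1 − 310/414 = 0.251, or 25.1%.
- At 25% in total: 310/0.75 = 413.3, rounded up to 414.
- At 25% per group: 155/0.75 = 206.7, rounded up to 207, and 2 × 207 = 414.

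**3. What 414 leaves if 20% are lost.** 414 × 0.80 = 331.2, about 331 in total or about 166 per group. That is about 21 more than the printed 310, so the mismatch is conservative against that figure.

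**4. Whether 310 is a sound base.** This decides how the mismatch may be described. For a one-tailed comparison of two means with SD 1:

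n per group = 2 × (z₀.₉₅ + z₀.₈₀)²/d² = 2 × (1.645 + 0.842)²/0.2² ≈ 309.1 with unrounded z values, so 310.

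The exact t calculation gives 309.8, also 310. So 310 is the requirement **per group**, or 2 × 310 = 620 in total. The article prints it as the total.

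**5. Power actually available at d = 0.2, one-tailed α = 0.05.** The normal approximation is Φ(d × √(n/2) − 1.645). Exact t values are alongside.

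| Per group | Situation | Normal approximation | Exact t |
|---|---|---|---|
| 155 | the printed requirement | Φ(1.761 − 1.645) = 54.6% | 54.5% |
| 165.6 (about 166) | 414 recruited, 20% lost | Φ(1.820 − 1.645) = 56.9% | 56.8% |
| 207 | 414 recruited, none lost | Φ(2.035 − 1.645) = 65.2% | 65.0% |

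For 80% power on these inputs with 20% dropout, the target would be 620/0.80 = 775, or 776 with equal groups.

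**The case against.** The strongest reply is that nothing is lost. The target exceeds the 388 that 20% dropout requires, a study may aim above its minimum, and a surplus of about 21 at follow-up biases no estimate and changes no analysis. Most of this stands. Against the printed 310 the mismatch costs no power, and it is a minor inconsistency. An unstated margin is conceivable, but the article mentions none and ties 414 directly to the 20% expectation, so the derivation still needs correcting. The exact match at 25% suggests that one figure was changed without the other; that is an inference about history, and the point does not depend on it.

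The reach of the figure is also fairly limited. It describes loss up to three months, so it should not be read as the loss affecting the knowledge outcome.

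Two stronger readings are tempting, and the document supports neither. A reader might infer that the trial can really absorb 25% loss. That holds only relative to the printed 310; on the stated effect, error rate and power, 414 falls short of 80% even with no loss. A reader might also infer that 414 is 26 too many and could be reduced to 388. That would treat 310 as an adequate total, which it is not.

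**Conclusion.** The point holds as an internal arithmetic inconsistency. 310 with 20% dropout gives 388, and 414 corresponds to 25%. The size is 26 participants, or about 5 percentage points of dropout (20% against 25.1%). The mismatch is minor by itself and conservative against the printed 310.

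This rests only on the article's own figures and on the usual rule of dividing by the retained fraction; adding the percentage does not rescue it. The power figures further assume equal groups, d = 0.2 and a one-tailed t-test at 0.05, all taken from the article. They show that neither 20% nor 25% dropout can be called a loss that leaves 80% power, because 310 is a per-group requirement.

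**What to change.** Keep 414 and make the dropout statement agree with it in one of two ways:

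- state 25% as the rate used to get from 310 to 414; or
- keep 20% as the expected rate and state that about 331 participants (about 166 per group) are expected at follow-up.

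Do not lower the target to 388, and do not present 25% as a tolerated loss that preserves 80% power. The 414 in the abstract can stay.

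In the same correction, say that 310 is the one-tailed requirement per group (620 in total), and restate the one-tailed power at d = 0.2: about 54% with 155 per group, about 57% with 166 and about 65% with 207.

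Reconciling the dropout rate costs one figure or one clause, and restating the power costs a further sentence or two. Neither changes recruitment, data collection or analysis. Recruiting towards 80% power on these inputs (about 775 to 776 with 20% dropout) would be a separate and much larger decision for the sponsor.
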